### **5.Interventions**

#### **5.1 Surgical and Anesthetic Method**

Both the experimental and control groups underwent flexible ureteroscopy with ureteral stent placement in the operating room. Following lithotomy positioning,

participants received either EA or sham EA 10 minutes prior to general anesthesia induction, with stimulation maintained until procedure completion.

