### **3.Study design**

This study is a randomized, single-blind, placebo-controlled, parallel-group, multicenter clinical trial with a superiority design, aimed at preliminarily evaluating the efficacy and safety of EA compared to sham EA in improving the success rate of UAS placement during first-stage RIRS. A total of 120 patients with urinary tract calculi requiring first-time ureteral stent placement under general anesthesia will be enrolled and rigorously randomized into the EA group or sham EA group.

Comprehensive clinical data will be prospectively collected and analyzed to establish a robust scientific foundation for optimizing therapeutic strategies in urolithiasis management.

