| Location of Stimulated Points          | Sanyinjiao (SP6),
Zhaohai (KI6), Taixi (KI3) | 3 mm lateral to the acupoints in the experimental group |
| Needling Depth                         | Approximately 10 mm-30 mm                       | 1-4mm                                                   |
| Deqi Sensation                         | Yes                                             | No                                                      |
| Actual Current Output                  | Yes                                             | No                                                      |

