## 6.Clinical observation index

### (1) Primary endpoint

The primary endpoint is the proportion of patients who achieved successful UAS placement and completed the first-stage RIRS without major intraoperative complications.

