### (2) Secondary endpoints

Secondary outcomes include: (1) Surgical duration, recorded in minutes from incision to closure; (2) UAS insertion resistance, measured with an IMADA50N push-pull gauge (calibrated monthly for accuracy); (3) Ureteral injury rate, assessed at UAS removal using the Post-Ureteroscopic Lesion Scale (PULS) by two blinded urologists, with a third resolving discrepancies; (4) Stone clearance rate, defined as the proportion of patients stone-free on CT two weeks post-surgery; and (5) AEs, tracked during surgery and for two weeks afterward, including acupuncture-related (e.g., bruising) and surgical (e.g., infection) events. These outcomes capture procedural efficiency, tissue safety, and recovery, with standardized tools and blinded assessments ensuring reliability. Training on PULS grading will be provided to assessors to maintain consistency.

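### Blinding is not stated for the operator or for whoever records the primary endpoint, although the endpoint arises under general anaesthesia with distinguishable needles in place, so it is open to performance and observer bias

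*Protocol*

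**What the plan says.** Section 3 describes the design: "This study is a randomized, single-blind, placebo-controlled, parallel-group, multicenter clinical trial with a superiority design". Neither this section nor the abstract says which party is blinded.

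Section 6 (2) contains the only statements about blinded roles. Ureteral injury is "assessed at UAS removal using the Post-Ureteroscopic Lesion Scale (PULS) by two blinded urologists, with a third resolving discrepancies", and the secondary outcomes as a group are described "with standardized tools and blinded assessments ensuring reliability".

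Section 6 (1) defines the primary endpoint as "the proportion of patients who achieved successful UAS placement and completed the first-stage RIRS without major intraoperative complications". It names no assessor and does not mention blinding.

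On timing, section 5.1 says that after lithotomy positioning "participants received either EA or sham EA 10 minutes prior to general anesthesia induction, with stimulation maintained until procedure completion". Section 5.3 puts the sham on the same timeline. Its comparison table gives six needles in the leg in both arms, with a needling depth of "Approximately 10 mm-30 mm" for EA and 1-4 mm for sham. EA needles are manipulated and carry current. Sham needles are not manipulated and are connected to a deactivated device.

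**The concern.** The sheath is passed while the patient is under general anaesthesia. If single-blind means that the patient is blinded, this does not protect the primary endpoint, because the patient can neither influence nor report whether the sheath went in. The knowledge that matters is that of the person passing the sheath, who chooses how hard to push and when to stop, and of whoever records the result.

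The background (section 1) notes that no quantitative threshold for excessive force exists. The protocol sets no criterion for successful placement or for abandoning it, so the decision is a judgement. An operator who knows the arm may persist longer in one arm or stop sooner in the other (performance bias). A recorder who knows it may score a borderline case differently (observer bias). An intention-to-treat analysis removes neither, and neither can be repaired once the operations are done.

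**Working it through.** **1. Who is stated to be blinded**

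| Role | What the protocol states |
|---|---|
| Patient | Not named; at most implied by single-blind |
| Operator passing the sheath | Nothing |
| Person recording the primary endpoint | No assessor named |
| PULS graders (secondary endpoint) | Blinded |
| Secondary outcomes as a group | Blinded assessments, in general terms |
| Draping, screening, or separation of acupuncturist and operator | Nothing |

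**2. Can the arms be told apart?** Inputs: needle length 40 mm (section 5.2); EA depth 10-30 mm and sham depth 1-4 mm (table in section 5.3). Exposed shaft = length minus depth.
- EA: 40 - 30 = 10 mm to 40 - 10 = 30 mm.
- Sham: 40 - 4 = 36 mm to 40 - 1 = 39 mm.

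The ranges do not overlap, so the difference can be seen by anyone with the legs in view. This uses the 40 mm length. The table in section 5.3 gives 4 mm, which does not fit its own EA depth; the two lengths must be reconciled.

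**3. The plan's own sample size, for scale.** With 90% against 75% and a 95% confidence interval of full width 0.28 (section 4):

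n per arm = 4 × 1.96² × (0.90 × 0.10 + 0.75 × 0.25) / 0.28² = 4 × 3.8416 × 0.2775 / 0.0784 = 54.4, so 55.

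The stated 55 per arm reproduces. One reclassified patient moves an arm's success rate by 1/55 = 1.8 points.

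**4. Size of the risk (illustration).** The documents give no bias size. Assumptions: true success 80% in both arms, 55 per arm, two-sided 5% level, apparent success raised in EA and lowered in sham by equal amounts. The rejection probability is the sum of binomial probabilities over all outcome pairs that the test calls significant.

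| Apparent success, EA / sham | Between-arm bias | Uncorrected chi-square | With continuity correction |
|---|---|---|---|
| 80% / 80% | 0 points | 5.1% | 2.7% |
| 83% / 77% | 6 points | 12.5% | 7.8% |
| 85% / 75% | 10 points | 26.2% | 18.4% |

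Nearly all the excess favours EA: in the last row, 26.1 of the 26.2 percentage points (uncorrected test). A 10-point gap is 5 points in each arm, or 0.05 × 55 = 2.75, about three patients per arm. With a 5-point shift in one arm only (80% against 75%), the figures are 9.7% uncorrected and 6.1% corrected.

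**The case against.** **Inference about the theatre.** The protocol does not say that the operator scores the primary endpoint or can see the needles. Ordinary surgical drapes may hide the legs. Sham patients have the same six needles connected to a device, and nothing shows that the presence of current is visible. This stands: a reader might infer that the operator works in plain view of the needles and knows the arm, but the text does not establish it. What remains is that the operator performs the step being scored, no other assessor is named, and no shielding is described.

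**Direction for insertion force.** A reader might infer that an unblinded operator would also move measured insertion force in favour of EA. The documents do not support this. The hypothesis is that EA relaxes the ureter and eases insertion, so pushing harder in EA or stopping early in sham would work against it. The direction is uncertain. Extra force could also turn an EA success into a failure, because the primary endpoint requires the absence of major intraoperative complications. This limits the bias but does not remove it.

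**PULS.** The graders are stated to be blinded. That they could see the legs is only a possibility, depending on where they work when they grade at sheath removal.

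**Assumed magnitude.** The base rate, the bias sizes and the test are all assumptions, and the protocol names no test. The continuity correction lowers the figures, as shown. Larger shifts would give larger figures, but 8 points in each arm is a 16-point gap, more than the planned 15-point effect, and is not a fair basis for the conclusion.

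**A separate analysis plan.** It could not cure this, since who is shielded in theatre is a matter of trial conduct.

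**Conclusion.** The point holds as a gap in the stated blinding of the primary endpoint. Followed as written, the protocol leaves the operator and the endpoint recorder free to know the arm, while the endpoint rests on a judgement made with distinguishable needles in place. It does not show that operators will be unblinded or that bias will occur.

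Under the stated assumptions, a between-arm bias of 6 to 10 points takes the false-positive rate from about 5% to about 12-26% without continuity correction, or from about 3% to about 8-18% with it. These figures show sensitivity and do not estimate the bias. The visibility argument depends on the 40 mm needle length and on the legs being in view.

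**What to change.** In sections 3 and 5.1:
- Name who is blinded, and include the operator, the theatre assistants and the person recording the primary endpoint.
- Have the acupuncturist cover or screen both lower legs, the leads and the stimulator display, identically in both arms, before the operator enters, and not disclose the allocation.

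In section 6:
- State that PULS graders do not see the legs or the stimulator.
- Record the operator's guess of the arm at the end of the procedure.

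Reconcile the two needle lengths in sections 5.2 and 5.3. The definition of the primary endpoint and the sample size need not change for this point.

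Cost: covers or a screen, a changed order of entry to theatre and one case report form item, with no extra staff, since an acupuncturist already gives the intervention in both arms. Downside: the acupuncturist must check and reach the needles under the cover, so access for the needle removal that sections 5.2 and 5.3 already require must be kept.

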## 5.2 EA Protocol for the Experimental Group

In addition to standard general anesthesia, EA was administered 10 minutes preoperatively and sustained intraoperatively. Sterile acupuncture needles (Hwato brand, 0.25 mm × 40 mm) were inserted at Sanyinjiao (SP6), Zhaohai (KI6), and Taixi (KI3). After lifting, thrusting, and rotating the needles for 30 seconds, an electronic stimulator (SDZ-II model, Hwato brand) was connected, delivering continuous wave at 50 Hz with current intensity adjusted between 1–5 mA (maximal tolerable level without pain). Licensed acupuncturists with ≥5 years of experience performed all interventions following standardized training on acupoint localization and needling techniques. Should any acupuncture-related adverse events occur, the acupuncture needles will be immediately removed. The specific acupoint localization protocols are as follows:

| Acupoint
(international
code) | Location                                                                                                                    | Angle and Depth                                                        |
|-------------------------------------|-----------------------------------------------------------------------------------------------------------------------------|------------------------------------------------------------------------|
| Sanyinjiao(SP6)                     | The medial side of the lower leg, 3 cun above the tip of the medial malleolus, posterior to the medial border of the tibia. | Insert the needle perpendicularly to the skin to a depth of 1-1.5 cun. |
| Zhaohai (KI6)                       | 1 finger-width medial to the ankle joint.                                                                                   | Insert the needle perpendicularly to the skin to a depth of 1.5-2 cun. |
| Taixi (KI3)                         | 2 finger-width medial to the ankle joint.                                                                                   | Insert the needle perpendicularly to the skin to a depth of 1-1.5 cun. |

## 5.3 Sham EA Protocol for the Control Group

Participants in the control group will receive sham acupuncture following the same procedural timeline as the experimental group. Needles will be inserted 3 mm lateral to the verum acupoints in non-meridian, non-acupoint regions using superficial needling (1–4 mm penetration depth) without needle manipulation (lifting, thrusting, or

rotating) . Following sham needling, the needles will be connected to a deactivated electroacupuncture device with internally short-circuited wiring to prevent current output. Should any acupuncture-related adverse events occur, the needles will be immediately removed. Sham acupuncture will be performed by licensed acupuncturists with  $\geq 5$  years of experience, who will undergo standardized training in sham acupoint localization and needling techniques prior to trial commencement.

The comparative characteristics of the experimental and control groups, including their shared features and key distinctions, are summarized in the table below:

| Program                                | Experimental Group                              | Control Group                                           |
|----------------------------------------|-------------------------------------------------|---------------------------------------------------------|
| Common Points                          |                                                 |                                                         |
| Stimulated Point Area                  |                                                 | Leg                                                     |
| Number of Acupoints/Non-Acupoints      |                                                 | 6                                                       |
| Number of Needles                      |                                                 | 6                                                       |
| Specifications of Needling Instruments | Length: 4 mm, Diameter: 0.25 mm                 |                                                         |
| Difference                             |                                                 |                                                         |
| Types of Stimulated Points             | Acupoint                                        | Non-Acupoint                                            |
| Location of Stimulated Points          | Sanyinjiao (SP6),
Zhaohai (KI6), Taixi (KI3) | 3 mm lateral to the acupoints in the experimental group |
| Needling Depth                         | Approximately 10 mm-30 mm                       | 1-4mm                                                   |
| Deqi Sensation                         | Yes                                             | No                                                      |
| Actual Current Output                  | Yes                                             | No                                                      |

## 6.Clinical observation index

### (1) Primary endpoint

The primary endpoint is the proportion of patients who achieved successful UAS placement and completed the first-stage RIRS without major intraoperative complications.

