## **Abstract**

**Introduction:** Retrograde intrarenal surgery (RIRS) is a primary treatment modality for urinary tract stones, and successful placement of the ureteral access sheath (UAS) is a critical procedural step. Preliminary studies have suggested that preoperative electroacupuncture (EA) may improve UAS placement success rates, reduce ureteral injury, and enhance stone clearance outcomes. This trial evaluates the efficacy and safety of EA as an adjunctive therapy in first-stage RIRS.

**Methods and analysis:** This multicenter, randomized, single-blind, sham-controlled trial will enroll 120 adult patients with upper ureteral or renal stones ( $\geq 10$  mm) scheduled for first-stage RIRS. Participants were randomly allocated (1:1) to receive either preoperative EA combined with general anesthesia or sham EA combined with general anesthesia across multiple treatment sessions. The primary outcome is the proportion of patients achieving successful UAS placement during first-stage RIRS. Secondary outcomes included operative time, resistance during UAS insertion, ureteral injury (assessed via the Post-Ureteroscopic Lesion Scale [PULS]), stone clearance rate at 2 weeks postoperatively, and adverse events (AEs) within 2 weeks postoperatively. Data will be analyzed using the intention-to-treat principle.

**Discussion:** This study will be the first randomized controlled trial (RCT) to investigate the efficacy of EA in improving both the success rate and safety of UAS placement during first-stage RIRS. The findings will provide high-quality evidence to support the integration of EA as an adjunctive therapy in clinical practice. Through comprehensive multidimensional assessments, this research will demonstrate the potential for broader application of EA in urolithiasis management. Further rigorously designed clinical trials will be essential to validate and refine this promising therapeutic approach.

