### **4.Sample size estimation**

Based on preliminary trial results demonstrating a 90% success rate of UAS placement in the EA group compared to 75% in the sham EA group, this study adopts a conservative estimate that EA will yield at least a 15% superiority over sham EA for sample size calculation. With a two-sided significance level of 0.05, a 1:1 allocation ratio between groups, and 0.28 confidence interval width, a total of 110 participants (55 in the EA group and 55 in the sham EA group) are required to detect this superiority. Accounting for a potential 10% attrition rate, the adjusted sample size is 120 patients.

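### The protocol gives two different primary endpoints: sheath placement alone in the abstract, aim and sample size, and a three-part composite in Section 6

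*Protocol*

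**What the plan says.** Four places in the protocol bear on the primary endpoint.

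- **Abstract:** "The primary outcome is the proportion of patients achieving successful UAS placement during first-stage RIRS".
- **Section 3, Study design:** the trial evaluates EA against sham EA in "improving the success rate of UAS placement during first-stage RIRS".
- **Section 4, Sample size estimation:** the planning rates are a "90% success rate of UAS placement in the EA group compared to 75% in the sham EA group".
- **Section 6, (1) Primary endpoint:** the share of patients who achieved "successful UAS placement and completed the first-stage RIRS without major intraoperative complications".

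The first three name one event, sheath placement. The fourth requires three things: the sheath is placed, the first-stage operation is completed, and no major complication occurs during surgery. The protocol does not say which definition governs. It also does not define *completed* or *major*.

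**The concern.** The two definitions classify some patients in opposite ways. Take a patient whose sheath goes in but whose operation is then stopped, or who has a major complication. That patient is a success under the abstract and a failure under Section 6. With both definitions standing in the protocol, the primary result can be computed in two ways, and nothing in this document prevents the choice from being made after the data are seen.

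The sample size is also tied to only one of the two. If Section 6 governs, the trial's planned precision was worked out for a different proportion.

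**Working it through.** **Side by side.** It might be thought that the abstract merely abbreviates Section 6. The rest of the protocol speaks against that. Sections 3 and 4 also refer to placement alone. The end of Section 1 lists placement success and procedural safety as separate key endpoints. The secondary endpoints in Section 6 already include ureteral injury and adverse events during surgery. Only the primary endpoint paragraph of Section 6 merges completion and complications with placement.

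**Reproducing the plan's figure.** Inputs from Section 4: p1 = 0.90, p2 = 0.75, two-sided 5% level (z = 1.96), full interval width 0.28 (half-width 0.14), 1:1 allocation.

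n per arm = z² × [p1(1 − p1) + p2(1 − p2)] / (half-width)²

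= 3.8415 × (0.0900 + 0.1875) / 0.0196 = 54.39, rounded up to **55 per arm, 110 in total**. This is the stated figure. The width at 55 per arm is 2 × 1.96 × √(0.2775/55) = 0.278. The sizing therefore rests on the placement rates.

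**What the composite would do.** The protocol gives no composite rate, so the following is an assumption: a share of placed patients fails the added conditions, and composite rate = placement rate × (1 − share lost). For example, 5% lost in both arms gives 0.90 × 0.95 = 0.855 and 0.75 × 0.95 = 0.7125. The width and n use the formula above. Power is the usual normal approximation with pooled variance under the null, where d = p1 − p2 and p̄ is the mean of the two rates:

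Φ{[d√n − 1.96√(2p̄(1 − p̄))] / √[p1(1 − p1) + p2(1 − p2)]}

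| Lost, EA / sham | Rates, EA / sham | Difference (points) | Width at 55 per arm | n per arm for width 0.28 | Power at 55 per arm |
|---|---|---|---|---|---|
| none | 90.0% / 75.0% | 15.0 | 0.278 | 55 | 54% |
| 2% / 2% | 88.2% / 73.5% | 14.7 | 0.289 | 59 | 50% |
| 5% / 5% | 85.5% / 71.25% | 14.25 | 0.303 | 65 | 44% |
| 10% / 10% | 81.0% / 67.5% | 13.5 | 0.323 | 74 | 37% |
| 5% / 10% | 85.5% / 67.5% | 18.0 | 0.310 | 68 | 61% |
| 10% / 5% | 81.0% / 71.25% | 9.75 | 0.317 | 71 | 22% |

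Two things follow.

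- **The width gets worse in every scenario.** A composite rate cannot exceed the placement rate. Both planning rates lie above one half, so moving them down towards one half raises the variance. There is almost no slack, since 54.39 was rounded up to 55.
- **The difference, and with it the power, can move either way.** It depends on whether the added failures are more common under EA or under sham.

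**The case against.** The strongest objection concerns what is built on the contradiction, since the contradiction itself is plain from the text.

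- **Loss of power.** A reader might infer that the composite must weaken the trial. That holds if the added failures are equally common in both arms. But Section 1 expects EA to reduce ureteral injury and make the procedure safer. If it does, the composite difference can exceed 15 points, as in the 5% / 10% row. Section 4 also sizes by interval width and states no power. The 54% for placement alone is a separate matter and is not caused by the endpoint mismatch. This objection stands.
- **Dilution of the mechanism.** A reader might infer that the added components reflect stone burden or lithotripsy and not ureteral relaxation. The protocol does not say so. Section 1 links perforation, avulsion and rupture to excessive force at sheath placement, so some added events belong to the effect under test. This objection stands.
- **Placement alone as the better endpoint.** It would count a sheath forced in at the cost of a ureteral injury as a success, and the composite guards against that. The documents do not settle which endpoint is better. They show only which one matches the rest of the protocol.
- **Definition behind the 90% and 75%.** Section 4 labels them as placement success but does not say how the preliminary trial defined it. The match to the abstract's endpoint rests on that label.
- **The analysis plan.** An SAP may exist and may name one endpoint. It would then disagree with part of this protocol, so the protocol still needs correcting. It does mean that selective reporting is a risk left open here, not something the documents show.

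**Conclusion.** The protocol is wrong as written: it states two primary endpoints that can classify the same patient differently, and it does not reconcile them. This follows from the text and needs no assumption.

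The stated 55 per arm reproduces exactly from the placement rates and the 0.28 width. Under the composite, with 2% to 10% of placed patients lost in both arms, the width at 55 per arm would be about 0.29 to 0.32, and 59 to 74 per arm would be needed to hold 0.28. Those shares are assumptions, because the protocol gives no composite rate.

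The effect on the treatment difference is not determined: 9.75 to 18 points across the scenarios, against the planned 15. The documents do not support a claim that the composite necessarily costs power.

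**What to change.** State one primary endpoint in the same words in the abstract and Sections 3, 4 and 6.

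- **Least change:** make the primary endpoint successful UAS placement at the first-stage operation, in all randomised patients. It agrees with the abstract, the aim and the sizing, so only the Section 6 paragraph changes. The composite becomes a secondary outcome, with *completed* and *major* defined.
- **If the sponsor keeps the composite as primary:** define both terms, align the abstract and Section 3, and restate the precision in Section 4 using justified composite rates for each arm.

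The cost is protocol wording and two definitions. Section 6 lists adverse events during surgery and graded ureteral injury, but no variable for completion of the operation and no severity grade for complications. If these are not already captured, they must be added to data collection.
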